**App Engagement Assessment**

The level of user engagement in the PuzzleWalk intervention will be measured through a Laravel-based backend system, which uses the Voyager administration system for data visualization and management (eg, frequency and duration of app use, step counts, and puzzle points). Time spent on the app in a minutes-per-day format will be calculated to represent each participant’s level of user engagement. These app engagement metrics will be aligned with accelerometer-derived PA and sedentary time to explore how engagement levels relate to daily behavior patterns. Although the study does not include a control group, a 7-day baseline measure will enable within-subject comparison over time. Additional sensitivity analyses will examine how variations in app engagement influence behavioral outcomes during the intervention period. Only activities related to the PuzzleWalk app will be accessed by the software developer and corresponding author as a principal investigator. Any identifiable information, such as email address, will be destroyed immediately upon completion of data collection to ensure participant confidentiality. Follow-up interviews will be conducted after the intervention ends to explore participants’ perceived acceptability, individual experiences (eg, satisfaction challenges), and factors that may have contributed to (dis-)continuation of the app use during and beyond the study. To secure and facilitate dataflow in the PuzzleWalk system, the user authentication process using Apple ID (ie, account credentials) will involve several key steps. First, the user initiates authentication through their Apple ID on the PuzzleWalk app. The app then obtains an authentication token from Apple, and forwards it to the backend server for verification with Apple’s authentication system. Once the token is verified, the backend server generates a session token, enabling the app to access the server application programming interface (API). This session token will facilitate secure API communication, allowing the backend server to interact with the database in real time and manage user requests efficiently (see Figure 3).

**Figure 3 figure3:**
[figure not shown]
PuzzleWalk system dataflow. JSON: JavaScript Object Notation; JWK: JSON Web Key.

### Data Analysis

Accelerometry data will be systematically analyzed by inspecting ranges and addressing missing values in accordance with the previously outlined validation protocol. The raw accelerometry output will be transformed into CPM values and processed using ActiLife software (ActiGraph). To account for the typical lifespan of mHealth interventions (eg, ≤3 months) [35], an intention-to-treat approach will be applied to ensure external validity. Baseline comparisons between autistic adults with and without mild intellectual disability, as well as between male and female autistic adults, will be conducted using independent *t* tests and chi-square tests. We will perform repeated measures ANCOVA to examine the changes in participants’ objective levels of PA and sedentary time before, during, and after the 6-week intervention, adjusting for baseline characteristics, including age, sex, mild intellectual disability, and BMI. Bonferroni post hoc tests will be performed if a significant difference is found between time points. Dependent variables will include light PA, MVPA, sedentary time (minutes per day), MVPA in bouts of >10 minutes per day, steps per day, and user engagement (eg, number of app login sessions and time spent on app use per day). Independent variables will be each time point and intervention. Pearson correlation analyses will be used to examine the relationship between the levels of PA, sedentary time, and user engagement during the intervention period. We will perform data analyses using SPSS v29 (IBM Corp), and the significance level will be set at *P*<.05 (2-tailed).

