### Sample and Recruitment Strategies

This pilot study acknowledges the potential for selection bias because individuals who volunteer for this PA-related study may already have a relatively high level of motivation to change their behavior. According to a priori power analysis using G*Power 3.1 [26], considering an α level of .05, an estimated effect size (f) of 0.2, an anticipated correlation of 0.4 among repeated measures, and 4 measurement levels of within-subjects factors, we project a total sample of 55 autistic adults to achieve a power of 0.9. To be eligible, prospective participants must (1) be adults aged 18 years to 55 years, (2) have received a formal diagnosis of ASD from a qualified medical professional, and (3) own and regularly use a compatible iPhone (iOS 14+ operating system). Android version development is underway, and its users will be invited to participate in future clinical trials. Individuals with moderate-to-profound intellectual disability or orthopedic conditions that significantly interfere with independent information processing or ambulation (eg, using a wheelchair or crutches) will be excluded from the study. These individuals may encounter challenges in engaging with the cognitive and physical aspects of the intervention, such as understanding verbal or written instructions, independently using the app, or meeting study requirements (eg, returning study materials to the research team). Therefore, only individuals who live semi-independently or independently, have autonomy for daily living, and are capable of making their own research-related decisions will be given an informed consent form to sign and subsequently invited to participate in the study. Future research shall explore adaptation strategies to make the mHealth interventions more accessible to a broader autistic population, including those with co-occurring moderate-to-profound intellectual disability.

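### Unless age and BMI are mean-centred, the repeated measures ANCOVA tests the time effect at age 0 and BMI 0, with power near 0.1 in place of the stated 0.9

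*Protocol article*

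**What the plan says.** The Data Analysis section names a repeated measures ANCOVA for change in physical activity and sedentary time before, during and after the six-week intervention, "adjusting for baseline characteristics, including age, sex, mild intellectual disability, and BMI". The software is SPSS v29 and the level is 0.05, two-tailed. The time effect is the gate to everything that follows: "Bonferroni post hoc tests will be performed if a significant difference is found between time points".

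The sample size in Sample and Recruitment Strategies rests on "an estimated effect size (f) of 0.2", "an anticipated correlation of 0.4 among repeated measures" and "4 measurement levels of within-subjects factors", from which "we project a total sample of 55 autistic adults to achieve a power of 0.9". That paragraph mentions no covariates. The Results section reports 69 enrolled as of July 2025, against a target of about 70.

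The article does not say whether age and BMI enter in raw units or centred, or how sex and mild intellectual disability are coded. It gives an eligible age range of 18 to 55 years but no mean or SD for age or BMI.

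**The concern.** With one arm and the same people at each time point, a baseline characteristic is constant within a person. It cannot confound that person's change; it can only describe who changes more. In a repeated measures general linear model, the within-person part therefore takes up such covariates as covariate-by-time terms. The test labelled time becomes the test that the intercepts of the change contrasts are zero, which is the expected change when every covariate equals 0.

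With raw age and BMI that point lies far outside an 18-to-55-year-old sample. The estimate is an extrapolation with a very large variance. The sample size calculation, by contrast, is for the average change across the sample. The named model tests that quantity only if the covariates are centred.

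Because this test opens or closes the pairwise comparisons, a real change of the planned size could be missed about nine times in ten. If change depends on age, the test can also reject when the average change is zero.

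**Working it through.** **Inputs from the article.** α = 0.05, f = 0.2, correlation ρ = 0.4, m = 4 measurements, N = 55 and power 0.9; 69 enrolled; four covariates.

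**Assumed inputs, not in the article.** Age mean 25-35 (SD 8-10); BMI mean 26-30 (SD 6-9); age and BMI uncorrelated. Illustration: age 30 (SD 9), BMI 29 (SD 7).

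**1. The article's own figure.** For a one-group within-subject test with sphericity, λ = f²·N·m/(1−ρ), with df 3 and 3(N−1).
- N = 55: λ = 0.04 × 55 × 4 / 0.6 = 14.67, power 0.903.
- N = 54: power 0.897.
- N = 69: λ = 18.40, power 0.960.

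So 55 is the smallest N that reaches 0.90, and the stated figure reproduces.

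**2. What the covariates do.** For each change contrast k, the model is d = β0k + β1k·age + β2k·BMI + (sex and intellectual disability terms) + error. The time test is β0k = 0 for all k. The variance of the estimated intercept is that of a plain mean multiplied by 1 + x̄′S⁻¹x̄, where x̄ and S are the covariate means and covariance matrix. For uncorrelated age and BMI the factor is 1 + (mean age/SD)² + (mean BMI/SD)². If change does not vary with the covariates, λ is divided by this factor and the error df become 3(N−5).

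**3. Power with raw age and BMI.**

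| Assumed age; BMI | Factor | λ, N=55 | Power, N=55 | λ, N=69 | Power, N=69 |
|---|---|---|---|---|---|
| 30 (SD 9); 29 (SD 7) | 1 + 11.11 + 17.16 = 29.3 | 0.50 | 0.080 | 0.63 | 0.089 |
| 35 (SD 8); 30 (SD 6) | 1 + 19.14 + 25.00 = 45.1 | 0.32 | 0.069 | 0.41 | 0.075 |
| 25 (SD 10); 26 (SD 9) | 1 + 6.25 + 8.35 = 15.6 | 0.94 | 0.110 | 1.18 | 0.127 |

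A correlation of 0.2 between age and BMI would raise the upper ends to 0.12 and 0.14. At N=55 in the illustration, raw age alone gives 0.13 and raw BMI alone 0.10.

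**4. Check by simulation.** With 6,000 trials per setting at the illustrative values (age limited to 18-55), and sex and intellectual disability included as effect-coded terms, raw age and BMI give 0.079 (N=55) and 0.081 (N=69). With all four covariates mean-centred, power is 0.901 and 0.959.

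**5. False rejection.** Assume that average change is zero but change differs by 0.02 to 0.03 outcome SD per year of age. The uncentred test then rejects about 10% to 17% of the time, against 5% to 6% when centred. The exact figure depends on the assumed slope and on how change is spread over the visits.

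**6. Coding of the binary covariates.** Suppose age and BMI are centred but sex and intellectual disability are effect-coded at ±0.5, with an assumed 20% having mild intellectual disability. That code has mean −0.3 and SD 0.4, so the factor is about 1 + (0.3/0.4)² = 1.56. Simulated power, with sex split 50:50, is 0.69 at N=55 and 0.80 at N=69. The test then concerns an unweighted average of the groups and not the sample average.

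**The case against.** A reader might infer that the plan prescribes uncentred covariates, or that its power is 0.08. The documents support neither. The Data Analysis section is silent on centring and lists no model terms, so a correct analysis is compatible with it. Naming SPSS does not settle which procedure or coding is used. The power figures rest on age and BMI distributions that the article does not give, and N=55 is not the enrolled number. All of this stands, and it is why the point is conditional.

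It can also be said that covariate coding belongs in an analysis plan or program code, and that a single-arm pilot aimed at feasibility and acceptability does not stand or fall on one F test. The first part has weight, but more than a missing detail is at issue. The article fixes the model, the covariates, the software and the gate, and it sizes the study for a within-subject test that this model delivers only under a condition it leaves out. As for the second, the article says it will examine change in activity and sedentary time by this test, and it claims a power of 0.9 for it.

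The power loss is calculated on the assumption that change does not vary with age or BMI. If change does vary, the uncentred test addresses a different quantity altogether, so this limit does not rescue it. The false-rejection figures rest on a further assumed slope and are secondary.

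**Conclusion.** The concern holds conditionally. The planned sample size is correctly computed for the average within-person change. The named ANCOVA tests that change only if its covariates are centred at their means. If raw age and BMI are entered, power for the planned effect falls from 0.90 to about 0.07-0.11 at N=55, and from 0.96 to about 0.07-0.13 at N=69. Enrolling 69 instead of 55 does not repair this.

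The size depends on the assumed age and BMI distributions and on change that does not vary with them. The direction does not: in any adult sample limited to ages 18-55, age 0 and BMI 0 lie far from the data, and power was low across the whole range examined. Under assumed age slopes with zero mean change, false rejection of about 10-17% is a further risk. The matter should be settled before the Phase II data are analysed.

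**What to change.** State that all four covariates, including the 0/1 indicators for sex and mild intellectual disability, are centred at their sample means before they enter the repeated measures ANCOVA. The time test then concerns the average change in the sample, and power stays at about 0.90 (N=55) or 0.96 (N=69).

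Alternatively, test time in a mixed model without covariate-by-time terms, and report covariate-by-time effects separately as moderators of change.

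Do not effect-code the unbalanced binary covariates. That tests an unweighted group average and brings power down to about 0.7 (N=55) or 0.8 (N=69) if 20% have mild intellectual disability.

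The cost is one sentence in the analysis plan. No further data are needed, and neither recommended option gives up meaningful power: four centred covariates take 12 of 162 error degrees of freedom at N=55, and power moves from 0.9032 to 0.9026.

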#### Phase II: Field Deployment of PuzzleWalk v2 mHealth System

Autistic adults who consent to participate in this single-arm clinical trial (NCT06566131) will receive study materials via the United States Postal Service, including a research-grade accelerometer/monitor (ie, ActiGraph CentrePoint Insight wristwatch), a cable charger, and study instruction sheets. Participants will also receive visual guidelines for wearing the monitor and returning study materials. The monitor wear guide will instruct the participants to wear the monitor comfortably on their nondominant wrist during waking hours, removing it only for water-related activities such as showering or swimming. Each night before bed, participants will record their monitor wear time in their tracking log and remove the watch during sleep. Reminders will be sent to participants every 3 weeks to 4 weeks to ensure uninterrupted use per the manufacturer’s recommendation for the monitor’s charging. The return guide will instruct participants to return the study materials by placing the monitor, charger, and tracking logs in a provided Ziplock bag, sealing them in a prepaid Priority Mailbox, and mailing them back to the research team via United States Postal Service (see Multimedia Appendix 2). Upon receipt, the research team will confirm the return by text message or email.

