Accelerometers will be programmed to collect data in 60-second epochs. Levels of activity intensity and sedentary time will be classified using activity counts per minute (CPM) cut point values: sedentary (<2860 CPM), light PA (2860-3940 CPM), and MVPA (≥3941 CPM) [30]. These cut point thresholds, established by Montoye et al [30], underwent cross-validation in both structured laboratory and free-living conditions with adults. A valid day will be defined as a minimum of 10 hours of accelerometer wear time a day. To be included in the data analysis, participants must have at least 3 valid days of accelerometer wear during each data collection period [31]. Despite the absence of a definitive consensus on the required number of valid days, previous research commonly accepts 3 days to 4 days as adequate for reliable estimation of one’s general patterns of PA engagement [32,33]. Nonwear time will be defined as 90 minutes of consecutive zero activity counts, with a 2-minute spike tolerance [34]. The accelerometers will be programmed to record PA and sedentary time at a default sampling frequency of 32 Hz. The CentrePoint cloud portal will streamline management and initial analysis of accelerometry data through a manufacturer-provided mobile app (ie, CentrePoint Connect app). Given the project’s timeline, participants will be required to install the app on their devices to remotely synchronize accelerometry data and prevent data loss before the device storage capacity (ie, 30 days or 512 MB) is reached. Processed raw accelerometry data will be securely managed and stored in the customizable CentrePoint cloud, and the research team will have a real-time overview of participant compliance (eg, at least 10 hours of accelerometer wear per day), data outcomes, and overall study progress.

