## Results

Phase I of the project, community-based participatory design workshops (n=9; 4/9, 44% women) was recently concluded. The findings revealed that key autism stakeholders highly valued the app’s self-monitoring and step tracking feature, leaderboard, and visual design. These features were perceived to enhance their perceived motivation for PA engagement and fostered a sense of friendly competition among users. Most stakeholders indicated that the app helped increase PA, reduce SB, and provide a sense of achievement. Autistic traits such as perfectionism and competitiveness reportedly influenced the level of engagement, sometimes enhancing motivation but occasionally causing discouragement due to the difficulty of the puzzle games. Overall, the app was viewed as a potentially beneficial tool for promoting PA and reducing SB in autistic adults (see Table 2). Data collection for Phase II of the project, which involves field deployment (approximate n=70), is currently underway and is expected to be completed in August 2025. As of July 2025, we enrolled 69 participants in the study. The results of this study will be shared in a subsequent publication.

**Table 2 table2:** Key findings of community-based participatory design workshops.

Activities	Key findings
Screening interviews and general inquiry on demographics, patterns of PA^a^ and SB^b^, and overall health among community stakeholders with autism	Most autistic collaborators were diagnosed with ASD^c^ during their early childhood by a medical professional and preferred communication via text messaging or email. Walking was the most preferred form of PA participation among collaborators with autism, but its frequency varied from “rarely” to “four times a week.”
Exploration of preferences and patterns of general technology use and its influence on PA and SB among autistic adults	Health-related mobile apps were generally seen as frustrating or unengaging due to complex interfaces or a lack of engaging features. Feedback highlighted the need for more intuitive functionality and fewer notifications. When it comes to gaming mobile apps, collaborators with autism tended to prefer simple or classic games rather than complex or time-intensive ones. Most collaborators with autism used their smartphones at home or work and typically kept them in a pocket when walking.

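### Sedentary, light and MVPA minutes per day are compared across weeks with no allowance for wear time, so any change in wear between periods biases the estimated change

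*Protocol article*

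**What the plan says.** In the Protocol article, the Data Analysis section gives the outcomes as follows: "Dependent variables will include light PA, MVPA, sedentary time (minutes per day". Bouted MVPA, steps per day and app engagement complete the list. The unit is printed after sedentary time; I read it as applying to light PA and MVPA too. The model is repeated measures ANCOVA, "adjusting for baseline characteristics, including age, sex, mild intellectual disability, and BMI".

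The PA and SB Assessment section assigns each minute to one of three classes by counts per minute: sedentary below 2860, light from 2860 to 3940, MVPA from 3941. Wear time appears there only as a criterion for admitting data: "A valid day will be defined as a minimum of 10 hours of accelerometer wear time a day", with at least 3 such days per period. Nonwear is a run of 90 minutes of zero counts, allowing a 2-minute spike.

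The Phase II section has the watch worn in waking hours, and each night "participants will record their monitor wear time in their tracking log and remove the watch during sleep". The App Engagement Assessment section confirms that there is no control group. Its sensitivity analyses concern app engagement, not wear.

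**The concern.** The cut points leave no gap, so every worn minute falls into exactly one class and the three classes sum to wear time. Participants decide how long they wear the watch, and any day from 10 hours up to the whole waking day counts as valid. If average wear differs between week 1 and a later week, at least one class must change even when behaviour has not. Steps and bouted MVPA are exposed in the same way.

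The direction depends on how wear changes. Less wear lowers sedentary and activity minutes alike, which flatters the app on sedentary time and counts against it on activity. A watch left on at night adds sedentary minutes, because only zero-count runs of 90 minutes are removed. A removal shorter than that scores zero counts and is also classed as sedentary.

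With a single arm, a wear change shared by participants cannot be separated from an effect of the app. The list of covariates is open, but only to further baseline characteristics. Wear in weeks 3, 5 and 8 is not one, and a standard repeated measures ANCOVA takes covariates that stay constant over time.

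**Working it through.** **1. The plan's own sample size.** The Sample and Recruitment Strategies section assumes "an α level of .05, an estimated effect size (f) of 0.2, an anticipated correlation of 0.4 among repeated measures". With four time points per participant, its conclusion is: "we project a total sample of 55 autistic adults to achieve a power of 0.9". For one group and a within-subjects F test, with sphericity assumed:

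- λ = f² × N × m / (1 − ρ) = 0.04 × 55 × 4 / 0.6 = 14.67, with 3 and 54 × 3 = 162 degrees of freedom.
- Power is 0.903 at N = 55 and 0.897 at N = 54, so 55 reproduces. At the 69 enrolled by July 2025 (Results section) it is 0.960.

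The sample size is not in dispute. It is used here only to size the planned effect.

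**2. The planned effect as a difference.** f is the SD of the four period means divided by the outcome SD.

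- Immediate, maintained change (0, 1, 1, 1): SD of the pattern = √0.1875 = 0.433, so the change is 0.2 / 0.433 = 0.462 SD.
- Linear change over weeks 1, 3, 5 and 8 (0, 2/7, 4/7, 1): SD of the pattern = 0.369, so the week 1 to week 8 change is 0.2 / 0.369 = about 0.54 SD.

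The documents give no SD. At an assumed 70 to 110 min/day these are 32 to 51 and 38 to 60 min/day.

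**3. The artefact.** False change in sedentary time = fall in mean wear × share of the lost wear that is sedentary. Both inputs are assumptions.

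| Fall in wear (min/day) | Share 60% | Share 70% | Share 50% to 100% |
|---|---|---|---|
| 30 | 18 | 21 | 15 to 30 |
| 60 | 36 | 42 | 30 to 60 |

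**4. Comparison.** The two are equal when SD = artefact / standardised effect.

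- 60-minute fall, immediate pattern: 36 / 0.462 to 42 / 0.462 = 78 to 91 min/day.
- 60-minute fall, linear pattern: 36 / 0.54 to 42 / 0.54 = about 66 to 78 min/day.
- 30-minute fall, immediate pattern: 18 / 0.462 to 21 / 0.462 = 39 to 45 min/day, below the assumed range. A 30-minute fall therefore does not reach the planned effect.

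**5. Effect on the test.** A simulation with no behaviour change assumed N = 69, ρ = 0.4, a 65% sedentary share, a linear fall in wear from week 1 to week 8, and an SD of 80 to 120 min/day. It used the one-way repeated measures F test without covariates. The time effect was significant at 0.05 in about 5% of trials with stable wear, 17% to 33% with a 30-minute fall, and 56% to 91% with a 60-minute fall.

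**6. Does percent of wear remove the bias?** Only if the lost wear has the same mix as the rest of the day. Suppose a 900-minute day has 585 sedentary minutes (65.0%) and loses 60 minutes, all sedentary. It becomes 525 of 840 (62.5%). The raw outcome falls by 60 minutes. The percentage falls by 2.5 points, or 22.5 minutes on a 900-minute day. The bias is smaller but not zero.

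**The case against.** The strongest reply is that the drift is hypothetical. The article gives no wear data and nowhere says that wear will decline. Check-ins and reminders, a live view of compliance with the 10-hour rule, and payment tied to consistent wear and submitted logs all act against a decline, and the 10-hour floor limits its size. This stands: a one-hour mean fall among valid days is an assumption, not an expectation. These measures encourage wear, however; they do not make it equal across the four periods.

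A second reply is that the article condenses a fuller document and that wear standardisation may be specified there. This has limited force, because the article does fix the outcome scale and the type of covariate.

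A third is that this is a pilot aimed at feasibility and acceptability, with controlled trials left for later and sedentary time one of several outcomes. A parallel fall in activity minutes would also be a visible warning. That lowers the severity but does not make raw minutes interpretable on their own.

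A reader might infer that wear will fall and produce a false benefit, or that a one-hour drift would imitate the whole planned effect. The documents support neither. The direction is not fixed, and equality with the planned effect needs an SD towards the low end of an assumed range.

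**Conclusion.** The point holds as a conditional bias and should be fixed. The plan analyses absolute minutes and steps, adjusts only for baseline characteristics, and uses wear time only as an entry filter. In a single-arm study, any shift in mean wear between periods then becomes part of the estimated change.

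Under the assumptions shown, a 30 to 60 min/day fall in wear would produce a false fall of about 18 to 42 min/day in sedentary time. That is a material part of a planned effect of 32 to 51 min/day (immediate change) or 38 to 60 min/day (linear change). The sedentary share, the SD and the fall in wear are all assumed, so these figures show scale and are not predictions. Night wear and short removals act in the opposite direction on sedentary time.

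**What to change.** Document the following before outcomes are analysed; data collection was expected to end in August 2025.

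- Analyse sedentary, light and MVPA time as a percentage of valid wear time, or as minutes standardised to a fixed-length day, within the planned ANCOVA.
- Use the tracking log to restrict each day to waking wear.
- Report mean wear time for weeks 1, 3, 5 and 8.
- Keep raw minutes per day as a sensitivity analysis.
- For steps, analyse steps per hour of wear. Alternatively, replace the ANCOVA with a linear mixed model that takes period-specific wear time as a time-varying covariate.

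Wear time and logs are already collected and the sample size stays at 55, so for the intensity classes this is a change to the outcome definition and some processing. The mixed model for steps is a change of model, not only of wording. The main results would be in percent of wear time, which is less direct to read than minutes. Some bias would remain if the lost wear is mainly sedentary time, which is why wear per period should be reported alongside.
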